### Standard-of-care (usual) transplant education (Arm 1)

During their transplant evaluation day, potential transplant candidates randomized to standard-of-care (usual) initial education will receive the standard transplant education and evaluation provided by SBMC. Family and friends are encouraged to accompany the patient to the evaluation. First, patients and their guests listen to and view a 90-minute slide presentation given by one of our trained transplant nurse coordinators. The presentation reviews:

• treatment options for chronic kidney disease, including LDKT and DDKT;

• the kidney transplant evaluation process;

• how the deceased donor waiting list works;

• the types of LDKTs and DDKTs. These slides succinctly review the benefits of LDKT, the workup of potential living donors, the types of living kidney donors, and alternative programs for LDKT;

• potential medical and psychosocial benefits and risks of kidney transplantation

• what to expect with the surgical procedure; and

• patients’ rights and responsibilities.

These topics must be included in the educational information provided to potential transplant candidates, as mandated by the Centers for Medicare and Medicaid Services [33].

After the presentation, potential transplant candidates are evaluated in private offices by members of the transplant team, including the transplant nurse coordinator, social worker, nephrologist, dietician, and financial coordinator. Potential transplant candidates meet separately with each transplant team member in a varying, unsystematic order, based on the availability of the team members. The research nurse or assistant also meets privately with each potential transplant candidate. Because the order in which potential transplant candidates meet with team members is unsystematic, the meeting between the research staff and the patient may occur at any point during the evaluation. The research staff member determines the patient’s eligibility for the study, obtains informed consent, and administers the initial questionnaires. The research nurse or assistant also sets an appointment date and time, at approximately one week after the transplant evaluation, for phone administration of follow-up questionnaires measuring knowledge and other outcomes.

### Intensive transplant education (experimental, Arm 2)

Potential transplant candidates who are cluster-randomized to intensive initial education (Arm 2) undergo the same education and evaluations as candidates in the usual education group. Additionally, study participants in the intensive education arm also undergo an intervention designed to increase knowledge of LDKT. This intervention is directed by the research nurse or assistant, who functions as a Transplant Educator. The intervention is based upon materials from the *Explore Transplant* series of kidney transplant education materials. When implemented in dialysis units, *Explore Transplant* has been shown to increase dialysis patients’ pursuit of DDKT and LDKT [40]. However, *Explore Transplant* has yet to be tested at a transplant center.

Our educational intervention consists of two parts, both implemented on the day of the transplant evaluation. First, study participants (together with any friends and family who accompanied them) view a 25-minute video, entitled “The experiences of living kidney donors”, from the *Explore Transplant* series of kidney transplant education materials [41,42]. This video, intended for potential transplant candidates, discusses how living donors came to their decision to donate; donors’ motivations and what they learned; facts about the donor evaluation, surgery, and recovery; risks to the living donors; and life after donation. The learning objectives of the video are to enable the viewer to understand the evaluation, surgery, and recovery process of living donors; learn possible risks that living donors face and how often these risks occur; learn the advantage of living donor kidneys versus deceased donor kidneys; and learn ways family member and friends can provide support to transplant candidates. The video features the stories of actual living kidney donors and presents accurate medical facts about LDKT, presented by medical professionals.

Second, after viewing the video, the study participants meet privately with the trained Transplant Educator for a fifteen-minute meeting to:

• Answer any questions that patients may have had, based upon what they saw in the video;

• Explore with patients their reasons for wanting a kidney transplant;

• Explore with patients their current situation with CKD/ESRD;

• Examine how the patients’ CKD/ESRD affects their family and friends;

• Answer any questions or concerns about transplant that the patient has;

• Review a brochure from *Explore Transplant*, “Why Kidney Patients Get Transplants/Why People Donate Their Kidneys”;

• Review a fact sheet from *Explore Transplant*, “Possible Risks to Living Donors”; and

• Review a fact sheet from *Explore Transplant*, “Living Donors’ Evaluation, Surgery, and Recovery”.

Because the order in which potential transplant candidates meet with team members is unsystematic, the viewing of the video and meeting with the Transplant Educator occur at any point during the transplant evaluation.

### Outcomes

#### ***Measurement timepoints***

After the transplant evaluation, we measure knowledge, readiness, self-efficacy, and decisional balance regarding transplant (DDKT and LDKT) (Table 1). To measure these characteristics, we administer telephone questionnaires to study participants at 1 week and 3 months after the transplant evaluation. These questionnaires are administered by research personnel who are not involved in participant recruitment and who are blinded to the study arm.

**Table 1 T1:** Data collection

	**Day of evaluation**	**1 week later**	**3 months later**	**12 months later**
**Transplant information**				
Demographic and medical characteristics	X			
Prior discussions with physicians regarding transplant	X			
Prior education regarding transplant	X			
Willingness to accept LDKT		X	X	
Actions to find living donors		X	X	
Placement on DDKT waiting list for transplant (and reasons for non-listing)				X
Mortality status				X
**Health literacy**				
Newest Vital Sign	X			
Single-item questions regarding use of surrogate reader and confidence with filling out forms	X			
**Outcomes**				
Knowledge of transplant		X	X	
Readiness to pursue transplant		X	X	
Self-efficacy regarding transplant		X	X	
Decisional balance regarding transplant		X	X	

We are unable to measure study participants’ “baseline” knowledge, readiness, self-efficacy, and decisional balance regarding transplant, prior to starting the evaluation. This inability stems from human subjects IRB restrictions that prevent us from administering questionnaires by telephone to persons who have not provided written informed consent. In addition, on the day of the actual transplant evaluation, obtaining individual written informed consent from up to six transplant candidates, prior to the delivery of any actual education, is also infeasible. Therefore, due to human subjects limitations and practical concerns, we are unable to obtain baseline measures (of knowledge, readiness, self-efficacy, and decisional balance regarding transpland and LDKT) prior to the start of usual or intensive transplant education.

#### ***Primary outcome: knowledge of LDKT at 1 week after the transplant evaluation***

The primary study outcome is knowledge of the benefits, risks, and process of LDKT, one week after the transplant evaluation. Knowledge is measured using a 20-item questionnaire that contains 12 true-false and 8 multiple-choice questions. This questionnaire is being used in other studies of LDKT and live kidney donation [42].

#### ***Secondary outcome: change in knowledge of LDKT at 3 months after the transplant evaluation***

As a secondary outcome, we also assess change in knowledge of LDKT three months after the transplant evaluation. Knowledge at three months is assessed using the same 20-item questionnaire that we use at 1 week after the transplant evaluation. LDKT knowledge “difference” scores will be calculated by subtracting the 1 week post-baseline LDKT knowledge scores from the 3 month post-baseline scores.

#### ***Other secondary outcomes***

The other secondary outcomes include: (1) readiness to pursue transplant and LDKT; (2) self-efficacy regarding transplant and LDKT; and (3) decisional balance regarding transplant and LDKT. These outcomes are also assessed by phone-administered questionnaires, at one week and three months post-evaluation. We will calculate self-efficacy and decisional balance “difference” scores by subtracting the 1 week post-baseline LDKT knowledge scores from the 3 month post-baseline scores.

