#### ***Self-efficacy (transplant confidence)***

We measure participants’ self-efficacy (transplant confidence), which reflects their confidence that they can enact and sustain a behavior change [45] (in this case, the behavior change is receipt of a transplant or LDKT). We assess study participants’ confidence in their ability to pursue transplant and LDKT in difficult situations. For transplant in general, we ask “How confident are you that you could get a transplant even if…” for eight items and scenarios, such as “…your friends and family were unsupportive of you getting a transplant”. Similarly, six self-efficacy questions focus upon LDKT and ask “How confident are you that you could get a living donor transplant even if…”, followed by items and scenarios such as “…you don’t know anyone who might be a living donor for you”. Responses are on a 5-point Likert scale from “Not at all confident” to “Completely confident”.

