#### ***Decisional balance (Pros and Cons of DDKT and LDKT)***

Decisional balance measures how patients are weighing the advantages and disadvantages (pros and cons) of transplant. We ask patients to rate the importance of possible positive and negative items related to patients’ decisions about DDKT and LDKT. We include 12 items regarding transplant in general and 12 items regarding LDKT. For each item, we ask, “How important is this statement to your decision about transplant/living donor transplant?” Sample statements include “I would live a longer life with a transplant” (Pro of transplant) and “I will feel guilty having someone donate to me” (Con of LDKT). Responses are rated on a 5-point Likert scale from “Not important” to “Extremely important”.

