#### ***Primary analysis***

To evaluate the effects of the intensive versus usual transplant education, upon LDKT knowledge one week after the transplant evaluation, we will compare overall knowledge scores between groups of candidates. These knowledge scores will be calculated by totaling the number of correct responses (range 0–20). We will compare knowledge scores between the usual vs. intensive education groups using the two-sample t-test with GEE. Randomization assignment (usual vs. intensive education) will be the independent variable. To adjust for any baseline characteristics that are unequally distributed between the two study arms, and to examine and control for the effects of confounders and other covariates, we will use multivariable linear regression models with GEE to determine differences in knowledge between the two study arms (usual vs. intensive education).

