#### ***Secondary analyses***

As a secondary outcome, we will also assess change in transplant knowledge from 1 week post-evaluation to approximately three months after the transplant evaluation. In this analysis, the outcome will be measured as “difference scores” (the 1 week knowledge score subtracted from the three month knowledge scores) using linear regression with GEE and adjusting for unequally distributed baseline characteristics [54].

We will determine the impact of the study intervention upon the other secondary outcomes: (1) readiness to pursue transplant and LDKT at 1 week post-evaluation; (2) self-efficacy regarding transplant and LDKT at 1 week post-evaluation; (3) decisional balance regarding transplant and LDKT at 1 week post-evaluation; and (4) changes in readiness, self-efficacy, and decisional balance regarding transplant and LDKT, from 1 week to 3 months post-evaluation. Self-efficacy, decisional balance, and change in self-efficacy and decisional balance are measured on a continuous scale, so they will also be analyzed with linear regression with GEE. Readiness to pursue transplant and LDKT will be analyzed as dichotomous outcomes, where the probability of patients being in Action or Maintenance vs. the probability of being in Pre-contemplation, Contemplation, or Preparation will be modeled with logistic regression with GEE. The tests for all secondary outcomes will also be adjusted for any unbalanced baseline characteristics.

Finally, to examine how key barriers to LDKT work alone and in combination with our intervention to impact LDKT knowledge, we will test the independent effects of race, previous actions taken to learn about transplant, and health literacy on knowledge at 1 week post-baseline. We will also test whether these variables interact with the intervention to effect knowledge of LDKT. We will model knowledge of LDKT as the dependent variable using multivariable linear regression models with GEE. To fit the models, we will use forward selection procedures where independent variables that are univariately significant at P < 0.20 will be eligible for inclusion in the multivariable model. Those variables significant at P < 0.05 in the multivariable models will be retained [55].

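### The change scores for self-efficacy and decisional balance subtract the wrong 1-week score (LDKT knowledge), contradicting the protocol's own aims and analysis sections

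*Protocol article*

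**What the plan says.** *Other secondary outcomes* gives the rule for two of the secondary constructs: "We will calculate self-efficacy and decisional balance “difference” scores by subtracting the 1 week post-baseline LDKT knowledge scores from the 3 month post-baseline scores".

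The section just before it, on change in knowledge at 3 months, has the same clause for knowledge, where it is right: "LDKT knowledge “difference” scores will be calculated by subtracting the 1 week post-baseline LDKT knowledge scores from the 3 month post-baseline scores".

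*Study aims* says the trial will look at how knowledge, readiness, self-efficacy and decisional balance each change between the two interviews. *Secondary analyses* lists as outcomes the "changes in readiness, self-efficacy, and decisional balance regarding transplant and LDKT, from 1 week to 3 months post-evaluation". It treats self-efficacy, decisional balance and their changes as "measured on a continuous scale, so they will also be analyzed with linear regression with GEE". That section spells out a subtraction for knowledge only.

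The scales are built differently:
- **Knowledge** is scored by "totaling the number of correct responses (range 0–20" (*Primary analysis*).
- **Self-efficacy** has eight general items and six LDKT items: "Responses are on a 5-point Likert scale from “Not at all confident” to “Completely confident".
- **Decisional balance**: "We include 12 items regarding transplant in general and 12 items regarding LDKT", also rated on five points.

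Table 1 shows all these measures collected at both 1 week and 3 months.

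**The concern.** The only written formula for the self-efficacy and decisional balance change scores names a 1-week score from a different instrument. A programmer who follows it does not obtain change in either construct.

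The error need not be neutral between arms. The protocol expects the intensive arm to score higher on knowledge at 1 week. A score that subtracts 1-week knowledge therefore inherits that arm difference with the sign reversed. The better the intervention does on the primary outcome, the lower the intensive arm comes out on these derived scores.

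There is also a question of record. An analyst who quietly uses the sensible definition departs from the published one, and an analyst who follows the published one reports something uninterpretable.

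**Working it through.** **1. The texts side by side.** The subtraction clause is the same in the knowledge section and in *Other secondary outcomes*; only the named outcome changes. *Study aims* and *Secondary analyses* both describe change within a construct. So the clause conflicts with two other sections, and nothing else in the article supplies a correct formula.

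**2. The plan's own figures.** The article states no figure for the change scores, so there is none to reproduce. The inputs that bear on the size come from *Power and sample size calculations*: 1-week knowledge 10–20% higher in the intensive arm, 250 patients per arm from about 100 evaluation days per arm (mean 2.5 per day), ICC 0.4 and type 1 error 0.05. No standard deviation is given.

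**3. Expected arm difference.** Let S be a self-efficacy or decisional balance scale, K the knowledge score, and δ the intensive-minus-usual difference in means.

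- Intended score, S(3 months) − S(1 week): expected arm difference δS3 − δS1. With no effect on S at either time, this is 0.
- Literal score, reading A, S(3 months) − K(1 week): expected arm difference δS3 − δK1. With no effect on S, this is −δK1.
- Literal score, reading B, K(3 months) − K(1 week): this is the knowledge change score again. The self-efficacy and decisional balance change scores would both equal an outcome already listed.

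**4. Size under reading A.**

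- 10–20% as a share of the 20-point range: δK1 = 0.10 × 20 = 2 to 0.20 × 20 = 4, so the arm difference is −2 to −4 points.
- 10–20% relative to a usual-arm mean M: δK1 = 0.10M to 0.20M, smaller because M is below 20. Assuming M = 10, 10% gives −1 point.

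**5. How often a nominal 5% test would reject under reading A with no true effect on the scale.** Design effect = 1 + (2.5 − 1) × 0.4 = 1.6; effective n = 250 / 1.6 = 156.25 per arm. SD of the literal score = √(SD_S² + SD_K² − 2ρ·SD_S·SD_K).

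The article gives neither the SDs nor whether items are summed or averaged. I therefore assumed knowledge SD 3–4, ρ 0–0.3, the ICC of 0.4 for the derived score, two-sided testing, and scale SDs of 0.9 (item mean), 5.5 (6-item sum), 7.5 (8-item sum) and 9 (12-item sum).

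Example, 6-item sum, knowledge SD 3, ρ = 0: SD = √(30.25 + 9) = 6.26; SE = 6.26 × √(2/156.25) = 0.709; 2/0.709 = 2.82; rejection probability Φ(2.82 − 1.96) ≈ 0.81.

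| Knowledge effect | Item mean | 6-item sum | 8-item sum | 12-item sum |
|---|---|---|---|---|
| 2 points | 99–100% | 74–90% | 55–69% | 44–54% |

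Across all four scalings, a 4-point effect gives 95–100% and a 1-point effect 15–87%. At 80% retention these fall by at most about 4 percentage points. With the intended score the rate is the nominal 5%.

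**The case against.** The strongest reply is that this is a copying slip rather than a chosen analysis, and that any reader can see what was meant. That is largely right. The intended quantity can be recovered from *Study aims* and *Secondary analyses*, and an alert analyst would probably use it. The analysis plan, which is not among the documents, may already state it correctly.

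A reader might infer more than the text supports:

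- **That the trial will report a false difference.** This needs the formula to be applied literally, against two other sections, and the 3-month score to be the scale's own. The sentence does not name that scale. Under reading B no scales are mixed and the −2 to −4 points do not arise.
- **That the distortion favours usual care throughout.** For self-efficacy a negative difference would look that way. Decisional balance combines pros and cons and the article does not define its direction, so no favoured arm can be named.
- **That the trial's main result is at risk.** The primary knowledge comparison, the sample size, the 1-week comparisons of the secondary constructs and the dichotomous readiness outcome do not use this formula.
- **That change scores should be replaced by another model.** The stated aim is change from 1 week to 3 months, and a wrong term in one formula is no argument against that aim.

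What remains after these concessions is that the sentence is complete, stands in an outcome definition, and gives no valid change score for either construct under any reading.

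**Conclusion.** The sentence is wrong as written and should be corrected. It names the wrong 1-week score, conflicts with *Study aims* and *Secondary analyses*, and is the only formula the article gives for these outcomes.

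The numerical consequence is conditional. If the formula is applied literally to each scale's own 3-month score, and the scale itself shows no effect, the expected arm difference is the 1-week knowledge effect with reversed sign. That is about −2 to −4 points on the share-of-range reading of the planning effect, and smaller on the relative reading. The rejection rates above also rest on assumed SDs, correlations and item scoring, and serve only to show that the distortion could be detectable.

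The reach is limited to the change outcomes of two secondary constructs. It is an internal inconsistency that needs correcting, not a flaw in the design or the primary analysis.

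**What to change.** Reword the one sentence in *Other secondary outcomes*. Each self-efficacy and decisional balance difference score should be that scale's 3-month score minus the same scale's 1-week score, computed separately for transplant in general and for LDKT. This agrees with *Study aims* and *Secondary analyses*, which need no change.

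If the analysis plan or the analysis programs carry the same clause, correct it there too and record the correction.

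The cost is one sentence. Both scores are already collected at both interviews, so data collection, sample size and the planned regression models stay as they are.

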#### ***Readiness to pursue DDKT and LDKT***

Readiness to pursue DDKT and LDKT are assessed using the Stages of Change, from Prochaska’s Transtheoretical Model [43,44]. For readiness to pursue DDKT, study participants choose whether there are in the Pre-Contemplation, Contemplation, Preparation, Action, or Maintenance stages (see Table 2 for descriptions of stages). Similarly, for readiness to pursue LDKT, study participants self-identify whether they are in Pre-Contemplation, Contemplation, Preparation, or Action (Table 2).

**Table 2 T2:** Statements that describe readiness (Stage of Change) for deceased donor and living donor kidney transplant

**Stage of Change**	**Readiness for deceased donor kidney transplant**	**Readiness for live donor kidney transplant**
**Pre-contemplation**	“I am NOT considering in the next 6 months getting a deceased donor transplant”	“I am NOT considering in the next 6 months getting a living donor transplant”
**Contemplation**	“I am considering taking actions in the next 6 months to get a deceased donor transplant”	“I am considering taking actions in the next 6 months to get a living donor transplant”
**Preparation**	“I am preparing to take actions in the next 30 days to get a deceased donor transplant”	“I am preparing to take actions in the next 30 days to get a living donor transplant”
**Action**	“I am undergoing transplant evaluation to get a deceased donor transplant”	“I am taking actions to get a living donor transplant”
**Maintenance**	“I am listed and waiting to get a deceased donor transplant”	None

To further assess readiness to pursue LDKT, we also assess Stage of Change regarding (1) asking a family or friend to consider living donation and (2) accepting an offer of a live donor kidney (among the subset of study participants who had received an offer of a live donor kidney).

